# Protocol of the optimal study: Optimization of polypharmacy in geriatric oncology - A randomized controlled trial

**DOI:** 10.1186/s12885-023-10812-7

**Published:** 2023-04-18

**Keywords:** Randomized controlled trial, Polypharmacy, Potentially inappropriate medication, Cancer, Rehabilitation, Quality of life

## Abstract

**Background:**

Polypharmacy is very common in older cancer patients and these patients are particularly vulnerable to drug-drug interactions and adverse drug reactions because they often receive chemotherapy and symptom-relieving agents.

**Methods:**

The primary aim of the randomized, controlled *Optimization of Polypharmacy in Geriatric Oncology (OPTIMAL)* trial is to test whether an advisory letter with the results of a comprehensive medication review conducted with the Fit fOR The Aged (FORTA) list to the caring physician in rehabilitation clinics improves the quality of life (QoL) of older cancer patients exposed to polypharmacy more than usual care. The FORTA list detects medication overuse, underuse, and potentially inappropriate drug use among older adults. In the oncology departments of approximately 10 German rehabilitation clinics, we aim to recruit 514 cancer patients (22 common cancers; diagnosis or recurrence requiring treatment in the last 5 years; all stages) who are ≥ 65 years old, regularly take ≥ 5 drugs, and have ≥ 1 medication-related problem. All necessary information about the patients will be provided to a pharmacist at the coordinating center (German Cancer Research Center, Heidelberg), who will perform randomization (1:1) and conduct the medication review with the FORTA list. For the intervention group only, the results are sent by letter to the treating physician in the rehabilitation clinics, who shall discuss medication changes with the patient at the discharge visit, as well as implement them afterwards and disclose them in the discharge letter to the general practitioner. The control group gets the usual care provided in German rehabilitation clinics, which usually does not include a comprehensive medication review but can include medication changes. Patients will be blinded, as they cannot know whether proposed medication changes were part of the study or part of usual care. Study physicians cannot be blinded. The primary endpoint will be the EORTC-QLQ-C30 global health status/QoL score, assessed via self-administered questionnaires 8 months after baseline.

**Discussion:**

If the planned study shows that a medication review with the FORTA list improves the QoL of older cancer patients in oncological rehabilitation more than usual care, it would provide the necessary evidence to translate the trial’s findings into routine care.

**Trial registration:**

German Clinical Trials Register (DRKS): DRKS00031024.

## Background

The number of older cancer patients in Germany is relatively large and it is expected to increase further due to demographic changes and trends towards improved cancer survival rates by adopting the best practice in cancer treatment and management [1]. In Germany, the majority of cancer patients receives at least 3 weeks of in-patient rehabilitation shortly after primary cancer therapy to support them in coping with functional impairments that may occur as a result of the cancer therapy [2].

The prevalence of multimorbidity and polypharmacy strongly increases with age, making treatment of older cancer patients complex and challenging. For example, although guidelines exist for the management of many major chronic diseases, adherence to these guidelines may lead to polypharmacy and adverse drug-drug and drug-disease interactions in the presence of multiple chronic conditions [3]. Older cancer patients are particularly prone to the unintended consequences of polypharmacy because they often receive chemotherapy and symptom-relieving agents, which may entail additional risk for drug-drug-interactions and adverse drug reactions [4].

The term “polypharmacy” is mostly defined by 5 or more concurrently prescribed drugs [5]. For example, every second colorectal cancer patient aged 65 years or older was exposed to polypharmacy in a German study, and polypharmacy was significantly inversely associated with overall and cancer-specific survival although potential confounding was well controlled by adjustment for all other major risk factors for poor cancer survival [6].

With an increasing number of prescribed drugs in general, the likelihood for potentially inappropriate prescribing (PIP) increases. PIP is an umbrella term for medication overuse, underuse, and the use of potentially inappropriate medication (PIM) in older adults. An assessment tool for all these three aspects of PIP is the Fit fOR The Aged (FORTA) list [7]. A German study applied the FORTA list and showed how common these medication problems are among older colorectal cancer patients aged 65 years and older [8]. The prevalence of PIM, medication over-, and underuse was 52.6%, 66.7% and 48.7%, respectively.

### Objectives

The aim of the OPTIMAL study is to test with a single-blinded, randomized, controlled trial (RCT) design, whether an advisory letter with the results of a comprehensive medication review conducted with the FORTA list to the treating physician in rehabilitation clinics improves the global quality of life (QoL) of older cancer patients exposed to polypharmacy more than usual care. Secondary endpoints will be QoL sub-domains, hospitalizations, falls, mortality, fatigue, frailty, and medication quality.

A further aim of the OPTIMAL study is to establish a biobank with blood sample based data (including biomarker and genetic data) and other data collected in this study to investigate risk and protective factors for the development and unfavorable course of cancer. The term “unfavorable course” is broadly defined and includes death, hospitalizations, concomitant diseases, symptoms and QoL, and difficulties in performing activities of daily living.

## Methods/Design

The trial protocol has been developed in line with the SPIRIT guideline (Standard Protocol Items: Recommendations for Interventional Trials) [9]. This manuscript is based on the trial protocol version 4.0 from April 7, 2023. At the time of submission of the trial protocol, recruitment for the OPTIMAL study is planned to start in June 2023 and to be completed within 3 years.

### Study design

The OPTIMAL study is a national, multicenter, prospective, single-blinded, randomized, controlled trial aiming to test the superiority of an intervention over usual care. Figure 1 shows the schematic flow-chart of the study. By applying a parallel group design, the participants are randomly assigned in a 1:1 ratio either to the intervention group or to the usual care (control) group.

**Fig. 1 Fig1:**
[figure not shown]
Flow-chart of the OPTIMAL study. Abbreviations: FORTA, Fit fOR The Aged

Recruitment is planned in approximately 10 rehabilitation clinics located all over Germany. The coordinating center is the Division of Clinical Epidemiology and Ageing Research, German Cancer Research Center, Heidelberg, which will not participate in the recruitment of study participants but will conduct follow-ups after the rehabilitation clinic phase of the study.

### Endpoints

The primary endpoint of the study is the change of the European Organisation for Research and Treatment of Cancer’s Quality of Life Questionnaire’s Core 30 items (EORTC’s QLQ-C30 [10]) global health status (GHS)/QoL score. The GHS/QoL score can change in the time between filling of the baseline questionnaire (which takes place in the first 1–2 weeks of the rehabilitation clinic stay) and filling of the 8-month follow-up questionnaire (which takes place in study month 8–9). The GHS/QoL score is based on the following two questions: “How would you rate your overall health during the past week?” and “How would you rate your overall QoL during the past week?”, both of which have a scale from 1 (“very poor”) to 7 (“excellent”). According to the EORTC-QLQ-C30 manual, the two numbers are being summed up, the sum is being divided by two and subsequently standardized to a scale from 0 to 100 points.

The following Table 1 lists all endpoints that will be examined in the OPTIMAL study and the time-points of their assessment. Secondary endpoints will be the change of medication quality (total FORTA score and its sub-scores [7]) from rehabilitation clinic admission to discharge in week 3, other time-points of assessments of the GHS/QoL score (at 4- and 12-month follow-ups, which take place in study months 4–5 and 12–13, respectively), the other domains of the EORTC-QLQ-C30 including physical and cognitive functioning as well as symptom scores that often reflect adverse drug reactions (nausea, constipation diarrhea), dizziness, fatigue, frailty, falls, hospitalizations, as well as overall, non-cancer, and cancer-specific survival [10–12].

**Table 1 Tab1:** Outcomes and their Operationalization

Outcomes	Ascertainment/Operationalization	Time of assessment				
		Week 3	Month 4–5	Month 8–9	Month 12–13	Year 1–10
Total medication quality	Total FORTA score	x		x		
Medication underuse	FORTA medication underuse sub-score	x		x		
Medication overuse	FORTA medication overuse sub-score	x		x		
PIM use	FORTA PIM use sub-score	x		x		
Global health status	EORTC-QLQ-C30 questions: 29 + 30		x	x (primary)	x	
Physical functioning	EORTC-QLQ-C30 questions: 1–5		x	x	x	
Role functioning	EORTC-QLQ-C30 questions: 6,7		x	x	x	
Emotional functioning	EORTC-QLQ-C30 questions: 21–24		x	x	x	
Cognitive functioning	EORTC-QLQ-C30 questions: 20,25		x	x	x	
Social functioning	EORTC-QLQ-C30 questions: 26,27		x	x	x	
Dyspnoea	EORTC-QLQ-C30 question: 8		x	x	x	
Pain	EORTC-QLQ-C30 questions: 9, 19		x	x	x	
Insomnia	EORTC-QLQ-C30 question: 11		x	x	x	
Appetite loss	EORTC-QLQ-C30 question: 13		x	x	x	
Nausea and vomiting	EORTC-QLQ-C30 questions: 14,15		x	x	x	
Constipation	EORTC-QLQ-C30 question: 16		x	x	x	
Diarrhoea	EORTC-QLQ-C30 question: 17		x	x	x	
Dizziness	Self-developed					
Fatigue	EORTC-QLQ-C30 questions: 10,12,18		x	x	x	
Physical fatigue	EORTC-FA12 questions: 1–5		x	x	x	
Emotional fatigue	EORTC-FA12 questions: 6–8		x	x	x	
Cognitive fatigue	EORTC-FA12 questions: 9–10		x	x	x	
Interference of fatigue with daily life	EORTC-FA12 question: 11		x	x	x	
Frailty	FRAIL-SCALE				x	
Falls	Frequency, self-reported				x	
Hospitalizations	Frequency, self-reported				x	
All-cause mortality	All deaths					x
Cancer mortality	ICD-10 codes C00-C97					x
Non-cancer mortality	All ICD-10 codes except C00-C97					x

Abbreviations: European Organisation for Research and Treatment of Cancer’s Quality of Life Questionnaire’s Core 30 items; EORTC-QLQ-FA12, EORTC’s Quality of Life Module Measuring Cancer Related Fatigue with 12 items; FORTA, Fit fOR The Aged; FRAIL-SCALE, Fatigue, Resistance, Ambulation, Illnesses, & Loss of Weight; ICD, International Classification of Diseases; PIM, potentially inappropriate medication

### Study population

The target population is older cancer patients (≥ 65 years), exposed to polypharmacy, who undergo in-patient rehabilitation in a cooperating clinic for at least 3 weeks. The target population will be representative for older, multi-morbid cancer patients in the German rehabilitation setting because it will be carried out as a multi-center study and the in- and exclusion criteria are restricted to the necessary minimum (e.g., by excluding only rare cancer sites, and by not excluding specific cancer stages or patients with specific cancer treatments).

In detail, the following inclusion criteria will be applied in the OPTIMAL study:

Diagnosis or recurrence requiring treatment of one of 22 selected, frequent cancers (International Classification of Diseases (ICD)-10 codes) in the last 5 years: esophagus (C15), stomach (C16), small intestine (C17), colorectal (C18-20), anus (C21), liver (C22), gallbladder/other biliary tract (C23-24), pancreas (C25), lung (C33-C34), malignant melanoma (C43), breast (C50), vulva (C51), cervix (C53), uterus (C54-55), ovary (C56), prostate (C61), kidney (C64), bladder (C67), Hodgkin lymphoma (C81), non-Hodgkin lymphoma (C82-C88), multiple myeloma (C90), and leukemia (C91-C95).Age ≥ 65 years.Exposure to polypharmacy, defined as ≥ 5 chronically, concurrently used active substances (including on-demand medication if used at least once per month). Food supplements (except vitamin D), homeopathic drugs, anthroposophical drugs, herbal drugs without systemic action and other non-systemic acting drugs (for local action in the skin, eyes, ears, nose or throat, only) are not counted because they do not cause (systemic) adverse drug reactions if they are not overdosed. This definition of “clinically relevant polypharmacy” has been published previously [13].At least 3 weeks of in-patient rehabilitation in a cooperating clinic are planned.Sufficient capabilities for informed consent.

The following exclusion criteria will be applied in the OPTIMAL study:

No written informed consent to participate.No sufficient mental and physical capabilities to fill self-administered questionnaires.No sufficient knowledge of the German language.Missing information needed to conduct the medication review with the FORTA list (medical diagnoses and drugs used at the start of rehabilitation).No medication related problem at baseline (FORTA score = 0).Missing baseline information needed for the primary endpoint (change in EORTC-QLQ-C30 GHS/QoL scale).

### Measures during the course of the study

The contacts with study participants during the course of the study and their scope is shown in Fig. 2.

**Fig. 2 Fig2:**
[figure not shown]
Contacts with study participants during the course of the study and their scope

#### Screening (before or at the start of rehabilitation)

Screening for eligible study participants will be done by a study nurse or a study physician via checking the patient’s files (which captures clinical diagnoses and current drug use) before or shortly after their admission to the rehabilitation clinic with a standardized screening checklist stating the in- and exclusion criteria.

#### 1st study visit for information about the study (week 1 of rehabilitation)

During the first appointment in the rehabilitation clinic, eligible patients will be informed about the OPTIMAL study by a study nurse or a study physician and will receive the printed study information and baseline questionnaire. They will have the opportunity to ask questions and will be given enough time to consider their participation. A written informed consent to participate in the OPTIMAL study will be obtained.

Study participants will be asked to fill the baseline questionnaire in the next 2 days. The questionnaires are used for the collection of important parameters (e.g. drug use, medical diagnoses, vaccinations, lifestyle factors, baseline levels of endpoint scales (e.g. EORTC-QLQ-C30), and information needed to be able to contact the study participants for the follow-ups (name, sex, birthday, address and phone number). A study physician/nurse should ensure that the study participant completely fill the questionnaire. Furthermore, the study nurse/physician will copy information about medical diagnoses and prescribed drugs from the patient’s files to the appendix of the standardized screening checklist. Towards the end of rehabilitation week 1, the study nurse/physician will mail the screening checklist, the signed informed consent form, and the patient’s questionnaire to the coordinating center.

#### Blood sampling (week 1 of rehabilitation)

Usually in the morning after the first visit, 38.6 ml blood will be collected in 6 tubes (1 × 2.6 ml EDTA plasma, 1 × 9 ml EDTA plasma, and 3 × 9 ml serum) from each patient. All tubes will be mailed to the laboratory of the coordinating center with DHL express while ensuring a temperature between 2 and 8 °C. The blood samples will be stored in the coordinating center in freezers at -80 °C to serve as a biobank for future research.

#### Randomization, blinding, and medication review by pharmacist (week 2 of rehabilitation)

The pharmacist in the coordinating center will check correct inclusion into the study and randomize the study participants 1:1 to the intervention and control group. Computer-generated randomization lists will be prepared by the pharmacist before study initiation with randomizer.at, which will be stratified by recruiting center using permuted blocks of random sizes. The block sizes will not be disclosed, to ensure concealment. The allocation sequence will be stored in a locker whose keys will only be available for the pharmacist and his/her deputy. The randomization numbers will be linked to the study participant’s IDs. The study participant’s IDs are used to label the informed consent forms, questionnaires, and all other study materials for a specific patient. The study materials will be packed for each study participant’s ID in the coordinating center and shipped to the rehabilitation clinics. Study participants will get their ID with the package containing the study materials after giving their written informed consent to participate in the study. Staff in the recruiting study centers and the study participants will not see the randomization lists or any randomization number at any time. Unblinding of study participants will be prohibited until end of study month 13 (end of time for collection of 12-month follow-up questionnaires).

The pharmacist in the coordinating center will further perform the medication review with the 4^th^ version of the FORTA list updated in 2021 [7]. Medical diagnoses and drug use obtained from two sources (patient’s medical files and patient’s questionnaires) will be combined to ensure a high completeness.

The use of the FORTA list will be done in two steps:

1st step: Each of the medical diagnoses will need to be checked. The FORTA list comprises the 30 most frequent medical diagnoses and a list of frequently used active substances for each diagnosis. The active substances have a rating from A (indispensable) to D (avoid). The pharmacist will then compare the present medication with the rated active substances in the FORTA list and rates each drug/diagnosis found as follows:

Appropriate use: The medication is indicated; a drug classified as A (indispensable) or B (beneficial) is prescribed.PIM use: The medication is indicated but a drug classified as C (questionable) or D (avoid) in the FORTA list is given despite available classes A (indispensable) or B (beneficial) alternatives.Underuse: An indication is not treated.

2nd step: Drugs not rated in the first step will then be checked and rated as follows:

Overuse: The medication is prescribed in the absence of an appropriate indication.Appropriate use: The medication is appropriately prescribed according to clinical guidelines for a disease not listed in the FORTA list, which is limited to 30 diseases.

The pharmacist will subsequently calculate the FORTA sub-scores for underuse, overuse, and PIM use for every patient and sum the three scores up to obtain the total FORTA score. Each medication underuse and overuse scores 1 point. Each PIM use scores 2 points.

For patients randomized to the intervention group, the pharmacist will fax an advisory letter to the study physicians stating suggested medication changes to overcome PIM use (by replacing drugs with a C or D rating by drugs with an A or B rating), underuse (by adding drugs with an A or B rating), and overuse (by withdrawal of drugs without indications). If the FORTA list suggests no medication changes, the letter will contain only the sentence: “No medication changes suggested”. For patients randomized to the control group, the letter will include the same sentence: “No medication changes suggested”.

Thus, the study physicians will be partly blinded because they cannot know the randomization group for patients for whom they received the sentence “No medication changes suggested” in the advisory letter from the coordinating center. However, they could still correctly guess that patients with medication changes suggested in the letter are in the intervention group. Thus, due to the nature of the intervention, the study physicians cannot be fully blinded and the study design is only a single-blinded study (only study participants will be blinded).

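### Allocation is concealed from clinics and participants, but not from the pharmacist who makes the final eligibility decision and scores the FORTA review behind it

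*Protocol article*

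**What the plan says.** All the relevant tasks fall to one role at the coordinating center. The section on randomization, blinding and medication review (week 2) assigns them as follows.

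- List preparation: "Computer-generated randomization lists will be prepared by the pharmacist before study initiation with randomizer.at".
- Custody: "The allocation sequence will be stored in a locker whose keys will only be available for the pharmacist and his/her deputy".
- Final entry check and allocation: "The pharmacist in the coordinating center will check correct inclusion into the study and randomize the study participants 1:1".
- Review: "The pharmacist in the coordinating center will further perform the medication review". The same section then has the pharmacist calculate the FORTA sub-scores and total for each patient.
- Identifiers: "The randomization numbers will be linked to the study participant’s IDs", and "Study participants will get their ID with the package containing the study materials after giving their written informed consent".

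The exclusion criteria under Study population include "No medication related problem at baseline", defined there as a FORTA score of 0. The abstract describes the pharmacist as the person "who will perform randomization (1:1) and conduct the medication review with the FORTA list".

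The safeguards stated are random, undisclosed block sizes, a locked list, and a rule that clinic staff and participants never see the lists or numbers.

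**The concern.** Concealment requires that whoever decides whether a patient enters cannot know which arm that patient would join. Here the last decision on entry belongs to the person who wrote the list and can open the locker. One of the criteria that person must apply, a FORTA score of 0, depends on a judgement only that person is described as making.

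Two things are at stake. First, a borderline patient could be judged in or out differently by arm, even without intent. There is a natural asymmetry: an intervention patient with nothing to change gets an empty advisory letter, whereas a control patient always gets one. Selective entry of this kind is not repaired by intention-to-treat analysis or by blinding participants. Second, the baseline FORTA score is the reference for the change in medication quality up to discharge, and it is scored by someone with access to the arm. The Discussion faults an earlier FORTA trial for its randomization and sets a high methodological bar for this one, so the point deserves closing.

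**Working it through.** **1. Which exclusions depend on the pharmacist's review.** Clinic staff screen from patient files with a checklist (Screening section), and no FORTA scoring at the clinic is described. Diagnoses and drugs from files and questionnaire are combined at the coordinating center, after the forms are mailed towards the end of week 1. A FORTA score of 0 can therefore be established only there, after consent. Missing review information is different: clinic staff copy the diagnoses and drugs themselves and can see gaps. The point rests on the FORTA criterion.

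**2. How much judgement is involved.** Underuse and overuse score 1 point each and PIM use scores 2. Overuse turns on whether an appropriate indication is present, and drugs for diseases outside the list are judged against clinical guidelines. A single point separates exclusion from inclusion.

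**3. Whether the arm can be known at that moment.** The lists exist before the study starts and are stratified by center, so their holder can read the next assignment for a center. The link between randomization numbers and participant IDs adds a second route if it exists when the forms arrive: IDs are issued after consent in week 1, and the inclusion check is in week 2. The article does not say when the link is made. The first route does not need it.

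**4. Whether the order protects against this.** The text points both ways.

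| Suggests review before randomization | Suggests randomization before review |
|---|---|
| The inclusion check is named before randomizing, and correct inclusion covers the FORTA criterion | The abstract and the week 2 section both name randomization before the review |
| The abstract describes the 514 as having at least one medication-related problem | A letter proposing no change is foreseen for intervention patients |

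The last entry matters because each scored item has a matching suggestion: add a drug for underuse, withdraw one for overuse, replace one for PIM use. If everyone with a score of 0 were removed before randomization, an intervention patient with nothing to suggest should hardly occur. These passages need reconciling. Either order leaves a problem: review after randomization means exclusions after allocation, and review before it still leaves the list with the assessor.

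**5. Whom the safeguards cover.** Undisclosed block sizes and keeping numbers from clinics protect against clinic staff and participants. The locker excludes everyone except the pharmacist and deputy. None restrains the pharmacist.

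**6. Figures.** The point rests on no figure. The plan's sample size reproduces:

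- Intervention SD: (16.15 / 8.55) × 14.41 = 27.22.
- Two-sided Satterthwaite t-test, difference 5.86, SDs 16.15 and 27.22, alpha 0.05: the smallest n with at least 80% power is 231 per group (power 0.801), so 462 in total.
- 462 / 0.90 = 513.3, rounded up to 514.

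The following is illustration only, on assumptions not in the document. Suppose a share f of intervention patients is selectively excluded and their mean change differs by g points from those kept. Then bias = f × g. With standard error √((16.15² + 27.22²) / 231) = 2.08:

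| f | g | Bias (points) | Share of 5.86 | Two-sided type I error |
|---|---|---|---|---|
| 2% | 5 | 0.1 | 1.7% | 0.050 |
| 5% | 10 | 0.5 | 8.5% | 0.057 |
| 10% | 20 | 2.0 | 34.1% | 0.161 |

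The span runs from negligible to material, and the article offers no basis for choosing a row.

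**The case against.** The strongest defence is that the people who screen, inform and consent patients are clinic staff, and concealment from them is sound. A reader might infer that allocation in this trial is simply not concealed. The article does not support that: sequences are computer-generated, blocks are random and undisclosed, and neither clinics nor participants see a number. The gap is confined to the final check at the coordinating center.

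A reader might also infer that randomization is stated to come before the review. It is not. The abstract only joins two tasks, the wording introducing the review can mean in addition rather than afterwards, and the flow-chart is not available here. The order is ambiguous. Similarly, the article does not say that IDs are already linked to allocations when eligibility is judged.

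A third tempting step is to put a number on affected patients. The Background prevalences (PIM 52.6%, overuse 66.7%, underuse 48.7%), if independent, give 0.474 × 0.333 × 0.513 = 0.081, or about 42 of 514. This should not be used. Independence is assumed, and without it the possible range is 0 to 33.3% (1 − 0.667). The source is a colorectal cohort not stated to be limited to polypharmacy, and the Background itself says inappropriate prescribing becomes likelier with more drugs. The 514 are patients to be randomized, so anyone removed earlier is not among them. The calculation also counts patients scoring 0, not borderline decisions.

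The consequences are bounded too. The primary endpoint is self-reported by blinded patients, and the FORTA endpoints are secondary and exploratory. The sensitivity analysis imputing outcomes for all randomized patients is a partial answer, but it cannot undo selection before randomization.

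Finally, the full protocol (version 4.0) is not shown and may set the working sequence. The concentration of roles, however, is stated explicitly in the article, so the narrower point stands.

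**Conclusion.** The point holds in limited form and should be fixed. Allocation is concealed from clinics and participants, but not from the person who makes the final eligibility decision and scores the criterion on which part of it depends. The article does not say that eligibility and the baseline FORTA score are recorded before allocation can be seen, and the no-change letter for intervention patients fits poorly with removing scores of 0 beforehand.

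This shows an opportunity for selective inclusion and for arm-aware baseline scoring, not that either will happen. Its size cannot be derived from the document. The conclusion assumes that the roles are carried out as the article describes, with no separation added elsewhere.

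**What to change.** In the section on randomization, blinding and medication review, state that:

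1. the pharmacist first completes and locks the FORTA review, the baseline score and the eligibility sign-off;
2. allocation is released only after that, one patient at a time;
3. the list is generated and held by existing coordinating-center staff with no role in review or analysis, or allocation is issued through the randomization tool already used;
4. no link from participant ID to allocation is available to the pharmacist beforehand.

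Reconcile the no-change letter for intervention patients with the FORTA exclusion, and state the order of review and randomization explicitly.

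The medical documentarist is a debatable choice as list holder. Under Data management & protection that role holds the pseudonymization code, so identity and arm would sit in the same hands. Another staff member or the randomization tool avoids this.

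The cost is a small procedural step within week 2. The sample size and analysis do not change. The article gives June 2023 as the planned start of recruitment; the change is best made before the first patient enters, because selective entry cannot be repaired afterwards.
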